## Abstract

Introduction. To date, radical surgery remains the best curative option in patients with early-stage lung cancer. In patients with small lung lesions, video-assisted thoracic surgery (VATS) should be increasingly chosen as a fundamental alternative to thoracotomy as it is associated with less postoperative pain and better quality of life. This scenario necessarily increases the need for thoracic surgeons to implement new localization techniques. The conventional near-infrared (NIR) indocyanine green (ICG) method demonstrated a significant limitation in deep cancer recognition, principally due to its intrinsic low-depth tissue penetration. Similarly, the lymph-node sentinel approach conducted by the ICG method was demonstrated to be inefficient, mainly due to the non-specificity of the tracker and the irregular pathway of pulmonary lymph node drainage. Our study aims to evaluate the effectiveness of Cetuximab- IRDye800CW in marking lung nodules and mediastinal lymph nodes. Methods and analysis. This study is defined as an open-label, single-arm, single-stage phase II trial evaluating the effectiveness of Cetuximab-IRDye800CW in detecting tumors and lymph-node metastases in patients with lung cancer who are undergoing video-assisted thoracic surgery (VATS). Cetuximab is a monoclonal antibody that binds, inhibits, and degrade the EGFR. The IRDye^®^ 800CW, an indocyanine-type NIR fluorophore, demonstrated enhanced tissue penetration compared to other NIR dyes. The combination with the clinical approved monoclonal antibody anti-epidermal growth factor EGFR Cetuximab (Cetuximab-IRDye800) has shown promising results as a specific tracker in different cancer types (i.e., brain, pancreas, head, and neck). The study’s primary outcome is focused on the proportion of patients with lung nodules detected during surgery using an NIR camera. The secondary outcomes include a broad spectrum of items, including the proportion of patients with detection of unexpected cancer localization during surgery by NIR camera and the proportion of patients with negative surgical margins, the evaluation of the time spawns between the insertion of the NIR camera and the visualization of the nodule and the possible morbidity of the drug assessed during and after the drug infusion. Ethics and dissemination. This trial has been approved by the Ethical Committee of Azienda Ospedaliera Universitaria Città della Salute e della Scienza di Torino (Torino, Italy) and by the Italian Medicines Agency (AIFA). Findings will be written as methodology papers for conference presentations and published in peer-reviewed journals. The Azienda Ospedaliera Universitaria Città della Salute e della Scienza di Torino, the University of Torino, and the AIRC Public Engagement Divisions will help identify how best to publicize the findings.

**Trial registration** EudraCT 202,100,645,430. ClinicalTrials.gov NCT06101394 (October 23, 2023).

## Background

Lung cancer is the leading cause of cancer deaths in the European Union (EU) (267,000 deaths/year) and the fourth most common cancer (321,000 new cases/year) [1]. To date, radical surgery remains the best curative option in patients with early-stage lung cancer. Moreover, cancer screening programs have led to frequent diagnoses of indeterminate lung lesions, many of which require surgical biopsy for diagnosis and intervention [2]. For example, available data showed that 5.9% of the European population over 15 years of age consumed at least 20 cigarettes per day (8.4% in the male population), and around 12.6% consumed less than 20. The recent lung cancer screening studies documented a prevalence of indeterminate pulmonary nodules as high as 50% in high-risk smokers, with a cancer detection rate in the overall screened population of 1% [3]. Fascinatingly, 69% of screen-detected lung cancers were detected at early-stage IA or IB [2]. Finally, studies on lung cancer screening, like the NELSON trial, show a 26% reduction in lung cancer deaths at ten years. The potential social impact of the present project is linked to establishing this screening program in Europe. One could estimate that if applied in the high-risk European population (i.e., high smokers), the screening could identify 3.5 million indeterminate pulmonary nodules, of which 250.000 are early-stage lung cancer [2]. Therefore, the use of the NIR-tracker we propose could consent to the use of minimally invasive surgery in this scenario as a diagnostic and therapeutic procedure. Consequently, it could determine the reduction of time to diagnosis, morbidity, mortality, and costs of postoperative care associated with more invasive surgical procedures.

To date, lung anatomical resection with lymphadenectomy remains the best curative option in patients with early-stage non-small cell lung cancer (NSCLC) [4]. Moreover, cancer screening programs have led to frequent diagnoses of indeterminate lungs, many of which require surgical biopsy for diagnosis and intervention [2]. Nevertheless, the increase in the utilization of minimally invasive procedures (e.g., video-assisted thoracic surgery -VATS- and robotic-assisted thoracic surgery -RATS-) remains mandatory in order to reduce the significant morbidity of classic surgery, the surgical trauma, to preserve organ’s function and to improve patient’s quality of life [5]. Nevertheless, minimally invasive surgery represents the surgical approach of choice in less than 40% of lung anatomical resections conducted in Europe [6]. One of the significant issues that hinder the application of VATS and RATS to most early-stage NSCLC patients is the difficulty in recognizing lung nodules located deep in the lung parenchyma and, consequently, not visible with the traditional camera system [7]. Indeed, VATS and RATS do not consent to manual lung palpation, making localizing the not superficial lung nodule problematic. Several approaches have been developed to enhance the localization of indeterminate lung nodules and decrease the time to diagnosis and rate of conversion to open surgery. Nevertheless, none of these are 100% sensitive or without complications, and they also have severe grades [8].

Numerous preoperative methods are being employed, including percutaneous CT-guided placement techniques, encompassing the use of micro-coils, hook-wires, and spiral-wires [8, 9]. These devices can support nodule localization during minimally invasive lung procedures; nevertheless, they could be easily displaced during patient transport and positioning, intraoperative atelectasis, single lung ventilation, and surgeon manipulation. Moreover, some locations of the lungs, such as the apex, near the diaphragm, and in the proximity of the mediastinum and great vessels. Furthermore, all these preoperative localization techniques require two different procedures, one for the CT-guided referral placement and one for surgical treatment. Finally, the rate of pneumothorax, hemorrhage, and subcutaneous emphysema are not insignificant, and these complications are mandatory to avoid in several sub-groups of patients. Other pre-operative methods encompass the use of dye marking by methylene blue or fluorescent [8]. Nevertheless, the accuracy of the staining of the targeted area is greatly affected by the time between tumor marking and thoracoscopy. In particular, the significant impact is on the difficulty of dye visualization during operation, limited information on lesion depth, and rapid diffusion of dye into the surrounding lung parenchyma between the time of injection and surgery. Of note, methylene blue has limited application in patients with anthracotic pigmentation. Moreover, these techniques require two procedures for diagnosis and treatment. Lastly, these procedures remain complicated by the risk of pneumothorax, bleeding, dye air embolism, cerebrovascular accident, and cases of lethal anaphylaxis to the dye of choice.

On the other hand, clinical pre-operative staging and surgical planning are based on preoperative images taken before surgery, either by computed tomography (CT), positron emission tomography (PET), or magnetic resonance imaging (MRI). These preoperative imaging assessments frequently underestimate lymph node involvement and secondary localizations. This results in an upstaging after surgical resection ranging from 9 to 24% in clinical Stage I lung cancer [10, 11]. Nevertheless, based on the direct injection of a tracker in the principal tumoral mass, the current intraoperative imaging system demonstrated a substantial limitation in lung cancer. This is principally due to the deeper location of the lymph nodes, usually profoundly engaged in normal fat tissue, and to irregular lymph node drain system in the respiratory region [12].

In this context, intraoperative fluorescence imaging can enhance the real-time identification of cancer cells during minimally invasive surgical procedures. This could overcome the difficulty of finding cancer nodules located deep in the lung parenchyma, not visible on the surface of normal, uninvolved tissue. The Near-infrared (NIR) fluorescence (700–1,000 nm) detection avoids biomolecules’ natural background fluorescence interference, which provides high contrast between the target and background tissues in small animals. NIR fluorophores have a more comprehensive dynamic range and minimal background fluorescence because of reduced scattering compared with visible fluorescence detection. However, the conventional near-infrared (NIR) indocyanine green (ICG) method demonstrated a significant limitation in deep cancer recognition, principally due to its intrinsic low-depth tissue penetration [13]. Similarly, the lymph-node sentinel approach conducted by the ICG method was demonstrated to be inefficient, mainly due to the non-specificity of the tracker and the irregular pathway of pulmonary lymph node drainage [12, 14].

The IRDye^®^ 800CW is an indocyanine-type NIR fluorophore with peak absorption at 775 nm and peak excitation emission at 796 nm. It provides a quantum yield of 9% and an extinction coefficient of 242,000 M-1 cm-1. Compared to other NIR dyes, the IRDye^®^ 800CW demonstrated enhanced tissue penetration [15].

Epidermal growth factor (EGF) is a 53–amino acid cytokine (6.2 kDa) that is secreted by ectodermic cells, monocytes, kidneys, and duodenal glands. EGF stimulates the growth of epidermal and epithelial cells. EGF, at least seven other growth factors, and their transmembrane receptor kinases play essential roles in cell proliferation, invasion, metastasis, neovascularization, adhesion, migration, differentiation, and inhibition of apoptosis. The EGF receptor (EGFR) family consists of four transmembrane receptors, which include EGFR (HER1/erbB-1), HER2 (erbB-2/neu), HER3 (erbB-3), and HER4 (erbB-4); and is commonly overexpressed in lung cancer [16]. Cetuximab is a monoclonal antibody that is able to inhibit and degrade the EGFR. Given intravenous infusion (IV), Cetuximab binds to the EGFR and stops the binding and activation of the downstream signaling pathways. Moreover, as we previously published, EGFR mutation is linked with skip-metastasis phenomena (i.e., pathologically proved mediastinal lymph node involvement in the absence of intrapulmonary or hilar lymph node disease) [17].

The IRDye800 conjugated with the clinically approved monoclonal antibody anti-epidermal growth factor EGFR Cetuximab (cetuximab-IRDye800) has shown promising results as a specific tracker in other cancer types (i.e., brain, pancreas, head, and neck) [18–20].

In detail, Cetuximab was incubated in the dark at room temperature with IRDye 800CW NHS Ester (LI-COR, USA) in 0,1 M potassium phosphate buffer (pH 7.8) for 2 h. The unconjugated dye was removed by size exclusion chromatography, using 0,9% NaCl as eluent, on an Amersham Biosciences AKTA FPLC System. The dye concentration was measured by absorption at 774 to confirm the number of fluorophore molecules conjugated to each mAb.

## Design

This study is defined as an open-label, single-arm, single-stage phase II trial evaluating the effectiveness of cetuximab- IRDye800 in detecting tumors and lymph-node metastases in patients with lung cancer who are undergoing minimally invasive thoracic surgery.

The trial has been registered to ClinicalTrial.gov with the registration number NCT06101394.

*Ethical committee referral number: 00136/2022*

## Methods

### Materials and equipment

We included patients diagnosed with NSCLC in clinical stage I (according to 8th Edition of TNM Staging System) who have been considered candidates for minimally invasive surgical resection after pre-operative assessment, including chest CT scans, PET, and respiratory function tests.

Regarding the age, we included patients ranging from 18 to 80. Patients with adequate bone marrow, kidney, liver, and heart function were included in the study. The included patients must have a PS ≤ 2, and potentially fertile female subjects must agree to use highly effective contraception throughout the study and for three months after the last dose of the study medication (According to CTFG recommendations related to contraception and pregnancy testing in clinical trials - Version 1.1–2020). The patients excluded from the study presented with characteristics like previous systemic treatments (chemotherapy, immunotherapy) for lung cancer, prior radiotherapy on lung or mediastinum, concomitant disorders that compromise the ability to adhere to the procedures of the protocol, Hb levels < 9 gm/dL, platelet count < 100,000/mm3, leukocyte count < 3000/mm3, absolute neutrophil count < 1500/mm3, electrolytes lower than the lower limit of normal per institution average lab values, TSH < 13 micro international units/mL, administration of an investigational drug within 30 days before the first dose of cetuximab IRDye800, MI, UA, heart failure, stroke or liver failure within 6 months before enrollment, previous infusional reactions to cetuximab or other monoclonal antibody therapies, evidence of QT prolongation, current therapy with antiarrhythmic agents including quinidine, procainamide, dofetilide, amiodarone, sotalol. Both pregnancy and present breastfeeding were considered exclusion criteria.

The study’s primary outcome is focused on the proportion of patients with lung nodules detected during surgery by NIR camera. The objective is to evaluate if cetuximab-IRDye800 can make visible lung nodules to the NIR camera through surgical procedures. The NIR camera used will be the EleVision™-Iridium VS3 (Medtronic, Dublin, Ireland). The detection of lung nodule NIR emission is registered in the first 5 min of the NIR camera activation during the surgery. The nature of the identified nodules (neoplastic or not) will be recorded during the surgery (sending the resected specimen for intraoperative pathology report (i.e., frozen section), later confirmed by the definitive pathology report) or 20–30 days after surgery according to the standard procedures in our center for the pathologic analysis of the operative specimens.

The secondary outcomes include a broad spectrum of items: the proportion of patients with unexpected cancer localization detected during surgery by NIR camera, the proportion of patients with negative surgical margins, the evaluation of the time spawns between the insertion of the NIR camera and the visualization of the nodule; and the possible morbidity of the drug assessed during and after the drug infusion.

The data will be collected from patient’s clinical records, entered in a secured password-locked web application, and then organized in a second password-locked database for easier data management. The data will include, at each relevant time point (Table 1), patient identification and anonymous demographic data, comorbidities, concomitant medications, vital signs, height and weight, Performance Status, adverse events (date of onset and resolution, maximum grade, relation to the study drugs), laboratory results, target, and non-target lesions assessments (dates and results), pulmonary function test, surgical details, post-operative data (complications, pain evaluate by NRS scale system, hospital length of stay) and final pathological staging. After the end of the protocol treatment, patients will be followed according to clinical practice (i.e. outpatient clinic follow-up visit with thorax and abdomen CT scans).

The expected rate of subjects lost to follow-up after surgery for early-stage lung cancer (as documented by large randomized clinical trials in this setting) is likely less than 5% and should not invalidate trial results. The data obtained during the trial will be treated under the applicable national and EU regulations.

Demographic and baseline characteristics will be presented for all patients. Discrete data will be summarized by frequencies and percentages. Continuous variables will be summarized using standard measures of central tendency and dispersion (mean and standard deviation or median and interquartile range).

The efficacy and safety analysis will be conducted on all patients undergoing surgery with cetuximab-IRDye800. A Hern’s Single-Stage Phase II design will be used. The study sample size has been calculated according to the efficacy endpoint. The efficacy analysis will be performed after the enrolment of 25 patients. The efficacy analysis will estimate the proportion of lung nodules correctly visualized by the NIR camera during surgery, with 90% confidence intervals (according to the 1-sided alpha error of 0.05). It is expected that cetuximab-IRDye800 will improve the proportion of NSCLC nodules detected intraoperatively from 40% (obtained employing white camera visualization) [7] to 70% by adding cetuximab-IRDye800. To conclude that the cetuximabIRDye800 is promising, the null hypothesis will be rejected if 15 or more patients out of 25 patients are correctly identified intraoperatively.

Toxicity will be recorded and classified according to the definitions of the NCI criteria “Common Terminology Criteria for Adverse Events (CTCAE),” version 5.0.

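### As printed, the TSH exclusion criterion rejects every patient with a value below 13, the normal range included, so it cannot be applied until it is reconciled with the full protocol.

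*Protocol article*

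**What the plan says.** The eligibility criteria are in the protocol article under Methods, Materials and equipment. The target population is introduced with "We included patients diagnosed with NSCLC in clinical stage I", in patients judged suitable for minimally invasive resection. The exclusions follow in one long sentence that begins "The patients excluded from the study presented with characteristics like previous systemic treatments".

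That sentence contains a run of laboratory limits: "Hb levels < 9 gm/dL, platelet count < 100,000/mm3, leukocyte count < 3000/mm3, absolute neutrophil count < 1500/mm3". Next come electrolytes below the institution's lower limit of normal, and then "TSH < 13 micro international units/mL".

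TSH is mentioned nowhere else in the article. Under Detailed procedure, the article says that blood tests, with history, clinical examination and imaging, are reviewed at screening against the inclusion and exclusion criteria. The TSH item is therefore presented as a working screening rule.

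**The concern.** An exclusion criterion names the values that keep a patient out. Here these are all values below 13, so the admissible set is 13 and above. The other laboratory items in the sentence keep out patients with low, abnormal results and leave normal results eligible. The TSH item does the opposite: it keeps out normal results and leaves only high ones eligible. The article gives no reason for wanting that. It does not require thyroid disease and does not link TSH to the tracer or to the surgery.

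As printed, the criterion leaves two outcomes, neither acceptable. If it is applied literally, almost all candidates are ineligible. If it is ignored, nearly every enrolled patient breaches the published criteria, and a reader cannot tell what thyroid screen was used.

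**Working it through.** The article states no figure that could be reproduced for this criterion, so the check is mainly one of logic. The arithmetic below only gives its size.

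**1. Logic of the list.** Set the laboratory exclusions side by side:

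| Item | Excluded | Still eligible |
|---|---|---|
| Haemoglobin | below 9 g/dL | 9 and above, normal values included |
| Platelets | below 100,000/mm3 | 100,000 and above, normal values included |
| Leukocytes | below 3000/mm3 | 3000 and above, normal values included |
| Neutrophils | below 1500/mm3 | 1500 and above, normal values included |
| Electrolytes | below the lower limit of normal | at or above that limit |
| TSH | below 13 micro-IU/mL | 13 and above only |

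TSH is the only row in which normal values fall on the excluded side. This needs one outside fact, that the upper limit of normal for TSH lies below 13. The article gives no range, so this is an assumption.

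**2. Size under assumed reference intervals.** Take a log-normal distribution whose central 95% is the interval (L, U):

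- mean of log TSH: m = (ln L + ln U)/2
- standard deviation: s = (ln U − ln L)/(2 × 1.96)
- share still eligible: 1 − Φ((ln 13 − m)/s)

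Worked example for 0.4–4.0: m = (−0.916 + 1.386)/2 = 0.235; s = 2.303/3.92 = 0.587; z = (2.565 − 0.235)/0.587 = 3.97; share eligible = 0.000036.

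| Assumed interval | 13 / upper limit | Share excluded | Share eligible |
|---|---|---|---|
| 0.3–3.5 | 3.7 | 99.997% | 0.0025% |
| 0.4–4.0 | 3.25 | 99.996% | 0.0036% |
| 0.4–4.5 | 2.9 | 99.988% | 0.012% |
| 0.5–5.5 | 2.4 | 99.96% | 0.038% |

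These shares describe people with ordinary thyroid function. A real candidate list would include some patients with raised TSH, so its eligible share would be larger.

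**3. What literal use would mean for accrual.** Analysis is planned for 25 patients: "The efficacy analysis will be performed after the enrolment of 25 patients". If a share q of otherwise suitable candidates has TSH of 13 or more, the expected number to screen is 25/q. With q assumed to be 2%, this is 25/0.02 = 1,250. With q = 0.5%, it is 25/0.005 = 5,000. Both values of q are illustrations and do not come from the article.

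**4. Does it touch the statistical design?** For X binomial with n = 25, the exact probability of 15 or more is 0.034 at the null proportion of 40% and 0.902 at the target of 70%. With a threshold of 14, the null probability would be 0.078. The rule of 15 or more therefore agrees with the interval statement "according to the 1-sided alpha error of 0.05", and none of these figures depends on the TSH criterion.

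**The case against.** The strongest reply is that this is a misprint in a condensed article. The eligibility text is running prose and not the numbered list of the approved protocol. If that protocol has a sound criterion, then recruitment, the enrolled population and safety screening are all unaffected. This stands as a limit on the consequences. The accrual figures hold only if the full protocol carries the same text and it is applied literally, which this document cannot show.

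It does not remove the point. The article states a screening rule that cannot work, and no other part of it corrects the rule. A fault in reading the PDF is unlikely, because the other inequality signs in the same sentence make sense.

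A reader might go further and infer that the sign has simply been reversed. That is the most obvious explanation, since the item follows a run of lower limits and a sign could have been carried over. But the number may be wrong instead, for example through a lost decimal point, or a statement of the required range may have been moved into the exclusion list. If the number is wrong, reversing the sign would leave a wrong limit in place.

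A reader might also infer that the trial's safety screen has failed. The article gives no purpose for the TSH item, so what it was meant to guard against is unknown.

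**Conclusion.** The criterion is wrong as printed and must be corrected. Read literally, it excludes all patients with normal TSH, given only that the upper limit of normal is below 13. Under the assumed intervals, at most about 0.04% of people with ordinary thyroid function would be eligible. The exact percentage depends on the log-normal assumption; the conclusion does not.

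The document does not establish which element is at fault: sign, number or placement. Nor does it establish that the trial's feasibility, population or safety has been compromised. The sample size, decision rule, error rate and power are unaffected.

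**What to change.** 1. Compare the TSH item with the approved full protocol on three elements: the inequality sign, the number with its unit, and whether it belongs in the exclusion list.
2. Correct whichever element is wrong in the article. No direction or limit is proposed here, because the document does not show which is right.
3. If the full protocol has the same error, amend it.
4. Check the screening records for any patient accepted or refused under the printed rule, and report any such case as an eligibility deviation or an incorrect screen failure.

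If only the article is affected, the cost is a short correction notice and a look through the screening records. If the full protocol is affected as well, an amendment is added. No sample size or analysis needs to be redone.

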### Detailed procedure

The researcher will screen the candidate for a lung nodule excision procedure for suspected lung cancer. All the patients screened for suspected lung cancer and evaluated for lobectomy are studied in the preoperative period and undergo a total body CT scan, PET scan, and respiratory function tests as suggested in European and International guidelines (in addition, shuttle test and cardiopulmonary function test are performed if deemed necessary according to the respiratory function tests) and chest or brain MRI if needed for further clinical necessities. The patient’s clinical history, vital signs, clinical exams, blood tests, and radiological exams will be examined to assess inclusion and exclusion criteria. The patient signs the written informed consent during the screening visit and is enrolled in the study. The pregnancy test will be performed 1 to 2 days before the infusion of the study drug.

The drug infusion will be performed 2 to 5 days before the surgery: the patients will receive 100 mg of cetuximab intravenously over 30 min to differentiate between an infusion reaction to the unlabeled cetuximab and a cetuximab-IRDye800 reaction and to preload the hepatic EGFR, and a dose of 50 mg of cetuximab-IRDye800 over 30 min to 1 h [3]. The doses were determined based on previous findings by other authors, showing that 25 mg/m2 provided the optimal tumor-to-background ratio. EKGs (electrocardiograms) will be performed at screening, 30 min post-infusion of the unlabeled cetuximab loading dose, two h post-infusion of the cetuximab-IRDye800, and follow-up on day 30. After the drug infusion phase, patients will undergo VAT resections of the lung nodule (between days 2 and 5 post-infusion). During post-surgery hospital stays and after discharge to home, patients will be treated and followed up according to clinical practice.

Patients will be monitored for toxicity and compliance with a clinical assessment after discharge. Moreover, subjects will be instructed before participation on the importance of reporting any symptoms (new or worsening), and/or any physical changes throughout their participation in the study. Morbidity or toxicity will be assessed during and after drug infusion, during and after a hospital stay, and during and after the control visits. If subjects discontinue before study completion, they will be encouraged to return for safety evaluations.

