Study drug will be discontinued for any of the following: Subject withdraws consent for the study, death attributed to study drug, serious systemic anaphylactic reaction (grade 3), or any serious rare reactions attributed to study drug.

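### The stated safety analysis set requires surgery with the tracer, so patients who stop at the unlabeled preload, or are infused but never reach surgery, fall outside it

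*Protocol article*

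**What the plan says.** The statistical text under Methods, Materials and equipment names a single population: "The efficacy and safety analysis will be conducted on all patients undergoing surgery with cetuximab-IRDye800". Just before this, baseline description has a wider scope: "Demographic and baseline characteristics will be presented for all patients".

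The same section lists the safety outcome among the secondary outcomes as "the possible morbidity of the drug assessed during and after the drug infusion".

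Under Detailed procedure, the timing is "The drug infusion will be performed 2 to 5 days before the surgery". Unlabeled cetuximab is given first, partly "to differentiate between an infusion reaction to the unlabeled cetuximab and a cetuximab-IRDye800 reaction"; the labeled tracer follows. The assessment window is wide: "Morbidity or toxicity will be assessed during and after drug infusion, during and after a hospital stay, and during and after the control visits". For early leavers, "If subjects discontinue before study completion, they will be encouraged to return for safety evaluations".

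The discontinuation paragraph at the end of that section stops study drug for withdrawal of consent, for death attributed to the drug, and for "serious systemic anaphylactic reaction (grade 3), or any serious rare reactions attributed to study drug".

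The article gives no other safety population, and none that is based on receipt of drug.

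**The concern.** A safety set should be entered through exposure. Here it is entered through an event, surgery with the tracer, that comes days after exposure and that a bad reaction can prevent. A patient must have come through the infusion well enough to be operated on with tracer on board before any infusion reaction counts.

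The preload makes this sharper. One of its stated purposes is to tell reactions to unlabeled cetuximab apart from reactions to the tracer. A patient who reacts to the preload and goes no further is exactly the case which that step is meant to identify. Without tracer, that patient cannot belong to the stated set, even if the operation goes ahead.

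At stake is the reported morbidity of the drug. With 25 patients, each one counts for 1/25 = 4.0 percentage points. Losses caused by a reaction can only move the result towards fewer events. The Ethics section relies on the tracer's adverse events resembling those of unlabeled cetuximab, so these are the events a reader will want counted.

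**Working it through.** **Step 1. Who is in the stated set?** The sentence has two conditions: surgery took place, and it was surgery with cetuximab-IRDye800. Applied to the possible courses:

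| Course after the first infusion starts | In the stated safety set? |
|---|---|
| Both infusions completed, operated on, with or without a reaction | Yes |
| Tracer infusion stopped part-way, still operated on | Arguable; may be included |
| Stopped at the unlabeled preload, no tracer, operated on | No |
| Infused, surgery not performed | No |
| Death after infusion, before surgery | No |

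In the last three rows the patient has been exposed and adverse events are recorded, but the patient is not in the set on which safety is to be analysed.

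**Step 2. The plan's own figure.** The design inputs are n = 25, reject at 15 or more, null rate 0.40, target rate 0.70, one-sided alpha 0.05.
- Exact alpha = P(X ≥ 15 | n = 25, p = 0.40) = 0.0344.
- Exact power = P(X ≥ 15 | n = 25, p = 0.70) = 0.902. The article states no power.

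The rule meets its stated alpha. It does not use the safety set, so a change to that set leaves it as it is.

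**Step 3. Effect on the reported rate (illustration).** Assume that all 25 enrolled patients are infused, and that k of them have a serious reaction and do not have surgery with tracer. Assume no serious reaction in the others. The rate as written is 0/(25 − k); among all infused it is k/25. Exact (Clopper-Pearson) 95% limits are shown; for zero events the upper limit is 1 − 0.025^(1/n).

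| k (assumed) | As written | Upper limit | All infused | 95% interval |
|---|---|---|---|---|
| 1 | 0/24 = 0% | 14.2% | 1/25 = 4.0% | 0.1% to 20.4% |
| 2 | 0/23 = 0% | 14.8% | 2/25 = 8.0% | 1.0% to 26.0% |
| 3 | 0/22 = 0% | 15.4% | 3/25 = 12.0% | 2.5% to 31.2% |

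**Step 4. How likely is it to arise?** Let q be the chance per patient of a reaction that prevents surgery with tracer. The article gives no value, so a range is assumed. The chance of at least one such patient among 25 infused is 1 − (1 − q)^25.
- q = 1%: 1 − 0.99^25 = 22%
- q = 2%: 1 − 0.98^25 = 40%
- q = 5%: 1 − 0.95^25 = 72%

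Here q is narrower than the rate of all serious reactions. It counts only those that end in no tracer or no surgery.

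**The case against.** The best defence is that the sentence is shorthand. The Abstract and the Design section describe the whole study population as patients undergoing thoracic surgery, so the analysis sentence may simply mean everyone treated. The infusion-based outcome, the wide toxicity window and the invitation to early leavers all suggest that the authors want these events. This stands as far as intent goes: nothing shows a deliberate wish to exclude anyone. It does not repair the text. The sentence defines an analysis set by surgery and by tracer, and collecting a patient's data does not place the patient in that set. Nor is this a detail left to an unseen analysis plan, because the article states the population itself.

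Several stronger readings are tempting and are not supported:
- **Any reaction that stops the drug removes the patient.** The discontinuation rule stops study drug; it does not cancel surgery. A patient who reacts after a full infusion and is operated on is included. One with a partial tracer infusion who is operated on may be.
- **The adverse events are lost.** They are recorded and graded by CTCAE; only the stated analysis omits them.
- **Every serious reaction leads to exclusion.** Only those that prevent tracer administration or surgery do. The discontinuation list gives triggers, not expected events, and patients with earlier infusional reactions to cetuximab or other monoclonal antibodies are not eligible.
- **Patients not operated on are replaced until 25 reach surgery.** The article describes no replacement. It ties the analysis to 25 enrolled patients, and enrolment occurs at consent, so the illustration starts from 25.

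It is also fair to say that safety is one of several secondary outcomes, with no test or threshold attached.

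**Conclusion.** Wrong as written, within limits. Exclusion from the stated safety set is clear in two cases: no tracer is given after the preload, or surgery does not follow the infusion, including death before surgery. When a reaction is the cause, reported morbidity is biased towards no harm, which conflicts with an outcome that the article itself starts at the infusion.

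The size is about 4 percentage points per such patient: with an assumed 2, none in 23 instead of 8.0%. The chance that at least one arises is 22% to 72%, if all 25 are infused and the per-patient chance of a reaction that prevents surgery with tracer is 1% to 5%. That rate is an assumption. If no such patient occurs, this bias does not arise. The point concerns a secondary outcome and leaves the primary decision rule unchanged.

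**What to change.** Replace the single sentence with two definitions. The safety set is all patients who receive any amount of unlabeled cetuximab or cetuximab-IRDye800, whether or not surgery follows. The set of patients undergoing surgery with cetuximab-IRDye800 is kept for efficacy only.

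The cost is one sentence in the analysis section. Toxicity is already assessed from the infusion onward, so no new data are needed. The sample size and the 15-of-25 rule stay as they are, and no dose or discontinuation rule is touched.
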